## Abstract

**Background:**

Recent findings indicated that mental disorders are associated with both an
up-regulation of negative affect and a down-regulation of positive affect
(PA) as distinct processes. Established treatment approaches focus on the
modification of problems and negative affect only. Experimental paradigms in
healthy samples and research on strengths-based approaches showed that
fostering PA may improve psychotherapy process and outcome. Specific and
easily implementable interventions targeting PA in treatment sessions are
scarce. Mental imagery was shown to be a promising strategy for boosting
positive emotional experiences.

**Method:**

The PACIfIC-study is planned as a longitudinal randomized-controlled trial in
the context of cognitive behavioral therapy, implemented at a German
outpatient training and research center. In the process analysis,
trajectories of PA over the first twelve treatment sessions will be examined
with weekly questionnaires. In the intervention analysis, a six-minute
positive mental imagery intervention to enhance PA will be developed and
tested. The intervention is implemented with loudspeakers at the beginning
of each session for a standardized induction of PA. The experimental group
will be compared to an active control group (neutral mental imagery) and
treatment as usual. Procedures in all treatment arms are parallelized. Main
outcomes after twelve sessions of psychotherapy will be psychosocial
resources, resilience and self-esteem (theory-driven), as well as
psychopathology and working alliance (secondary outcome). Multilevel
modeling will be conducted to address the nested data structure.

**Conclusion:**

Study results may have implications on the consideration of positive
constructs in mental disorders and the implementation of strengths-based
interventions in psychotherapy.

Treatments like cognitive behavioral therapy (CBT) have shown effectiveness for
various mental disorders (e.g. Hofmann et al., 2012). However, there is a lack of knowledge about basic processes in
mental disorders and psychotherapy. Affect dysregulation is recently discussed as a
factor for the maintenance of psychopathology. Affect is defined as the subjective
experience of an emotional state and is differentiated by its valence (Hofmann, 2016). Positive and negative affect
are assumed to be correlated, but separate constructs (Larsen et al., 2017; Watson et al., 1999). Dysfunctional up-regulation of negative affect (NA) is a
common feature in mental disorders (Aldao et al., 2010) and is successfully modified by CBT (Boumparis et al., 2016; Sauer-Zavala et al., 2012). In contrast, the impact of positive affect (PA) in
psychopathology and psychotherapy is not well established. Regarding this research
gap, we designed the Positive AffeCt and mental Imagery In the process of Cognitive
behavioral therapy (*PACIfIC)*-study.

## PA and Psychological Processes

PA is characterized by various emotions and moods with a subjective pleasant
valence. According to the broaden-and-build theory of positive emotions, PA
initiates a multistage upward spiral process (Fredrickson, 2001; Garland et al., 2010). In particular, research findings from healthy samples showed
that PA leads to a broadening of attention as well as thought and action
repertoires. Positive mood inductions in experimental paradigms increased
visuospatial attention as well as information processing (Phaf, 2015; Pourtois et al., 2017; Vanlessen et al., 2016). High PA was related to better performance in category building
and creativity tasks (Baas et al., 2008;
Nadler et al., 2010). Observational
and experimental studies showed that such broadening, in turn, was associated
with a reciprocal increase of psychosocial resources, resilience and mental
health (Garland et al., 2010; Griffith et al., 2021). The
broaden-and-build theory, therefore, hypothesized that an increase in PA will
lead to higher levels in these specific variables. Hence they may help to
evaluate interventions that target an increase of PA. Brief descriptions of
these constructs are presented in the following: Psychosocial resources were
defined as positive and functional aspects of a person or his/her environment
(e.g. optimism, social support; Taylor & Broffman, 2011). Previous findings indicated moderate to high
correlations between different constructs and the possibility to assess a
generic perception of inherent resources (Goldbach et al., 2020; Taylor & Broffman, 2011; Victor et al., 2019). Psychological resilience was defined as the potential to
successfully adapt to adversities and stressors (Davydov et al., 2010). Previous studies found that resilience is a
dynamic trait, which is both influenced by internal and external experiences and
changeable by purposeful interventions (Connor & Davidson, 2003; Mealer et al., 2014). Self-esteem is an important part of mental health and was
defined as the degree, a person positively consider his/her characteristics or
abilities (Brown, 2007). Baseline
parameters and trajectories of self-esteem and PA were strongly related in
observational and intervention studies (Garland et al., 2010; Wood et al., 2003). Most concepts have focused on a global evaluation of
self-esteem rather on specific facets (Rosenberg et al., 1995).

## PA in Psychopathology and Psychotherapy

Carl et al. (2013) pointed out that the
down-regulation or dampening of PA is an independent process in mental
disorders. In a prospective paradigm, baseline anxiety and depressive symptoms
were related to lower rates of daily positive emotional reactivity and decreased
levels of PA in the subsequent 14-day period (Carl et al., 2014). Specific analyses found decreased levels of PA
for various mental disorders (Cohen et al., 2017; Eisner et al., 2009;
Thompson et al., 2016). These
findings support the idea to consider and foster PA by psychotherapeutic
interventions. Concurrently, classical CBT treatments had only small effects on
PA in patients with major depression, *g* = 0.41,
*p* = .001, and anxiety disorders, *g* = 0.37,
*p* = .001 (Boumparis et al., 2016; Wilner Tirpak et al., 2019).

An established approach to foster positive constructs in psychological treatments
is resource activation. The activation of patients’ strengths and resources is
regarded as a change mechanism in psychotherapy and was significantly associated
with patients’ PA and treatment outcome in CBT sessions (Flückiger et al., 2009; Mander et al., 2013). Observer ratings showed that successful CBT
sessions were characterized by higher levels of resource activation and PA,
particularly at the beginning of treatment sessions (Gassmann & Grawe, 2006; Smith & Grawe, 2003). Moreover, Chui et al. (2016) found that higher initial PA of patients in
psychotherapy sessions lead to both more PA of therapists and better rated
post-session collaboration. Although these studies indicate the feasibility to
increase PA in psychotherapeutic settings and its promotive influences on
symptom improvement and working alliance, economical strategies that directly
targeting PA are lacking.

## Mental Imagery as a Strategy to Increase PA

Mental imagery is defined as “representations and the accompanying experience of
sensory information without a direct external stimulus” (Pearson et al., 2015, p. 590). Compared to other
interventions, mental imagery was found to be more effective in evoking emotions
(Holmes et al., 2009; Holmes & Matthews, 2010; Schubert et al., 2020). Recent research
approaches compared the imagination of positive versus neutral contents to
differentiate its affective impact (Grol et al., 2017). In clinical settings, most studies of positive mental imagery
were conducted as single interventions to promote PA in patients with major
depression: these trainings were associated with reduced depressive symptoms and
anhedonia, as well as increased optimism, positive self-referent cognitions and
behavioral activation in clinical samples (Blackwell et al., 2015; Dainer-Best et al., 2018; Ji et al., 2017;
Renner et al., 2017). Alternatively,
positive mental imagery has also been discussed to enhance anxiety (Wallace & Alden, 1997) and trigger
dissociation (Brewin et al., 2010).
Another analysis by O’Donnell et al. (2017) showed that positive mental imagery training in individuals
with high hypomanic experiences led to a dysfunctional amplification of positive
mood. Thus, while there is substantial evidence that fostering PA may be a
promising intervention strategy also in psychotherapy, we do not know whether
the systematic implementation of positive mental imagery has a beneficial impact
on psychotherapy process and outcome.

Specific analyses found important factors influencing the promotion of PA in
mental imagery: practicing mental imagery repeatedly (Blackwell et al., 2015; O’Donnell et al., 2017), including various sensory modalities (Holmes et al., 2008), imaging personally
relevant situations, aspects or perspectives (Quoidbach et al., 2009) and employing a field perspective (Grol et al., 2017).

## Current Study

The dysregulation of PA is a prominent and distinct factor in psychopathology and
should be focused in CBT. Higher experience of PA may broaden patients’
receptivity in treatment sessions and may enable goal-related approaching
behaviors. However, there is a massive lack of knowledge about PA in the
therapeutic process. To the best of our knowledge, no study has attempted to
activate PA via an economical intervention in CBT sessions.

Within the *PACIfIC*-study, both a process and an intervention
analysis will be conducted. In the process analysis, we will examine the course
of PA and NA in the first twelve sessions of CBT treatments. Therefore, primary
outcome in the process analysis will be the slope of PA and NA. Further measures
of resource activation, working alliance and psychopathology after each of the
twelve sessions will be included in the process analysis to analyze their
relation to PA (within and between sessions).

In the intervention analysis, we will examine the effects of a six-minute
positive mental imagery intervention during an early phase of psychotherapy. The
aim of this micro-intervention is to foster patients’ in-session PA, which may
lead to increased levels of subjective resources, resilience, and self-esteem
(theory-driven outcome) as well as improvements in psychopathology and working
alliance (secondary outcome). Changes in the theory-driven outcome variables are
expected due to the specific effects of increased PA according to the
broaden-and-build theory of positive emotions (Fredrickson, 2001). Changes in the secondary outcome variables are
expected due to found effects of resource activation and shared positive
emotions in treatment (Chui et al., 2016;
Flückiger et al., 2009). Patients
will be randomized into one of three parallel treatment arms with a 1:1:1
allocation: CBT + positive mental imagery micro-intervention (PMI), CBT +
neutral mental micro-intervention (NMI), or treatment as usual (TAU). Two active
mental imagery micro-interventions are planned to differentiate the specific
effect of a PA induction within treatment sessions. The study serves the
following objectives:

To explore the trajectories of PA and NA in an early phase of CBT
treatment.To develop and test the feasibility of a brief intervention to promote PA
in psychotherapy sessions.To analyze the impact of this intervention on the therapeutic process
between and within CBT sessions and intermediate outcomes.

We hypothesize that PA will increase, while NA will decrease during the first 12
sessions of therapy. According to the specific effects postulated by the
broaden-and-build theory of positive emotions, we further hypothesize that
patients in the PMI will show higher in-session PA and higher levels of
subjective resources, resilience, and self-esteem compared to the other
conditions.

## Method

### Design

Figure 1 displays a SPIRIT chart of the
planned study design. The study is a randomized controlled implementation trial
with three parallel treatment arms using a 1:1:1 allocation ratio. A blocked
randomization with blocks of variable length conducted by a random-number
generator (random.org) will be performed. Block length will be determined
randomly (9, 12 or 15 units), before conditions will be randomized within all
blocks separately. An independent research assistant will develop the block list
and conduct the randomization. Patients will be randomized to one of the
following arms: CBT + positive mental imagery induction (PMI), CBT + neutral
mental imagery induction (NMI) and TAU. All arms include an individual CBT
treatment. A cross-therapist design in which any therapist can deliver all three
conditions is applied. Randomization will be focused on patients only, so that
therapists will not see a fixed number of patients per condition. However, we
expect that the block randomization will enable an approximately equal number of
patients in all conditions per therapist. All participants are blind to the
conditions and specific hypotheses. According to the CONSORT statement
concerning the criteria of a pragmatic randomized trial (Zwarenstein et al., 2008) therapists and study coworkers
conducting the information meetings are not blind to allocation. Researchers
involved in data collection and evaluation will be blind to condition labels. An
independent researcher will analyze study data with non-identifying codes of the
conditions. The study includes a longitudinal design with an initial diagnostic
phase (four to five sessions) and the following twelve psychotherapy sessions.
Outcome for the process analysis will be gathered directly after each treatment
sessions. In the intervention analysis, assessments will be made every forth
session: at the start of treatment (pre), after fourth (mid-4), after eighth
(mid-8) and after twelfth treatment session (post-12). In addition, videotapes
of treatment sessions 2, 5 and 8 will be analyzed with an observer rating.

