### Participants

#### Patients

A total of 120 patients will be recruited at the Center of Mental Health and
Psychotherapy (CMHP), an outpatient training and research center for CBT at
Witten/Herdecke University, Germany. General inclusion criteria will be as
follows: (1) psychotherapy outpatient, (2) at least one mental disorder
according to DSM-5 criteria, (3) at least 18 years of age. General exclusion
criteria will be as follows: (1) current diagnosis of a severe episode of
major depressive disorder, (2) suffering from a psychotic disorder, (3)
suffering from substance use disorder, (4) current episode of (hypo)mania,
(5) current suicidal risk, (6) extensive experiences with guided mental
imagery interventions (two or more interventions in prior treatment
settings), (7) insufficient German language skills, (8) currently receiving
another psychological treatment. Prescribed medications for anxiety or
depressive disorders do not lead to exclusion from the study. The presence
of comorbidities does not result in exclusion from the study.

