#### Therapists

20-25 therapists will be recruited at the CMHP. All therapists have at least
a master’s degree in psychology. Both, licensed CBT therapists and
therapists in advanced CBT training will take part in the study. Trainee
therapists have at least one year of clinical experience before they start
treatments in the CMHP. Parallel to the study, trainee therapists take part
in 600 hours of practice-based workshops as a part of CBT training protocols
in Germany. Therapists participate in 90-minute supervision in small groups
on a weekly basis (general clinical supervision, not study-specific). Every
therapist in the CMHP will be informed about study procedures in small group
meetings of approx. 30 minutes conducted by [name].

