### Standard Procedure at CMHP

Adult patients with various types of mental disorders receive treatment by
approximately 20 licensed CBT therapists resp. trainee therapists. The CMHP has
eight rooms for providing psychotherapy. All rooms are fully equipped with video
and audio recording. Computer-assisted psychometric assessments during therapy
are standard procedures at the CMHP and regularly reviewed by staff members.
Personal and treatment-specific data is managed with a software called AmbOS. To
promote data quality, fixed schedules of assessments for patients and therapists
were included. Patients interested in a CBT treatment have a first phone contact
and a one-session consultation with a licensed therapist. They are then listed
on an internal waiting list (with currently on average six months waiting time).
Patients are contacted by a therapist and invited to a standardized diagnostic
phase. The diagnostic phase includes four to five sessions with the following
order: exploration and treatment consent, Structured Clinical Interview for
DSM-5 Disorders (SCID; Beesdo-Baum et al., 2019), biographic work, situation analysis. After the diagnostic
phase, a CBT treatment according to the German health system is offered.

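### Blocks of 9-15 that ignore the therapist do not control arm balance within therapists who see about 5-6 patients each, so the balance per therapist that the protocol expects is not supported

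*Protocol article*

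**What the plan says.** The Design section of the protocol article describes a trial "with three parallel treatment arms using a 1:1:1 allocation ratio". Block length is chosen "randomly (9, 12 or 15 units), before conditions will be randomized within all" blocks. On therapists it says: "Randomization will be focused on patients only, so that" "therapists will not see a fixed number of patients per condition". The next sentence nevertheless says that the authors "expect that the block randomization will enable an approximately equal number of" patients in each condition for every therapist.

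The numbers needed to test that expectation are in other sections. Under Patients: "A total of 120 patients will be recruited at the Center of Mental Health and" Psychotherapy (the power paragraph says up to 120). Under Therapists: "20-25 therapists will be recruited at the CMHP". Standard Procedure at CMHP gives a compatible figure: "approximately 20 licensed CBT therapists resp. trainee therapists".

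The Discussion then relies on the design. Innovations lists the cross-therapist design as a way to deal with therapist effects, and Bias Minimization says it is used to minimise them. The Statistical Analysis section has a three-level model: sessions in patients, patients in therapists.

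**The concern.** A permuted block balances the arms over the sequence it is applied to. Here that sequence appears to be the centre's list of patients. One therapist's patients are a small subset of that list, spread over many blocks, and nothing in the scheme forces that subset to be balanced. If blocks do not deliver balance per therapist, the sentence in Design states a property the trial does not have.

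Two things are at stake. First, a therapist with no patient in an arm gives no within-therapist comparison involving that arm. The PMI-NMI comparison matters most, because the Current Study section includes the two imagery arms to isolate the specific effect of inducing positive affect. Second, therapists range from trainees to licensed practitioners, so differences between them are plausible, and the Discussion credits the cross-therapist design with handling them.

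**Working it through.** **Inputs from the protocol.** 120 patients (Patients); 20-25 therapists (Therapists); three arms at 1:1:1 and blocks of 9, 12 or 15 (Design). One centre-wide list is inferred from randomisation being on patients only and from the absence of any therapist stratum.

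**The plan's own figure.** The protocol gives no number for balance per therapist. Its only calculated figure, the sample size of 78, reproduces: noncentrality 0.15² × 78 × 4 / (1 − 0.50) = 14.04 with 6 and 225 degrees of freedom gives power 0.801, and 77 gives 0.795. It does not bear on this point.

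**Caseload.** 120/20 = 6.0; 120/24 = 5.0; 120/25 = 4.8 (20 therapists with 5 patients, 5 with 4). All are below 9.

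**At least one empty arm, therapist with n patients.**
- Independent allocation, (3·2^n − 3)/3^n: n = 6 gives 189/729 = 25.9%; n = 5 gives 93/243 = 38.3%.
- Random draw from an exact 40/40/40 list, [3·C(80,n) − 3·C(40,n)]/C(120,n): n = 6 gives 24.4%; n = 5 gives 36.8%; n = 4 gives 54.4%. For 25 therapists: (20 × 36.8% + 5 × 54.4%)/25 = 40.3%.

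Exact overall balance therefore improves on pure chance by only about 1.5 percentage points.

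**No PMI or no NMI patient.** [2·C(80,n) − C(40,n)]/C(120,n): n = 6 gives 16.3%; n = 5 gives 24.9%; n = 4 gives 37.4%. For 25 therapists: (20 × 24.9% + 5 × 37.4%)/25 = 27.4%.

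**Simulation of the stated blocks** (4,000 trials per setting, near-equal caseloads, random assignment to therapists):

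| Therapists | At least one empty arm | Arm counts within 1 | Spread of 3 or more |
|---|---|---|---|
| 20 | 24.3% | 13.2% | 36.0% |
| 24 | 36.8% | 38.2% | 36.8% |
| 25 | 40.3% | 39.8% | 35.9% |

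The chance that every therapist covers all three arms is 0.3% or less.

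**Sensitivity of the empty-arm share to unstated assumptions.**
- One patient per therapist per round: 25-41%.
- Unequal caseloads (each patient goes to a therapist at random): 34-48%.
- Each therapist's patients consecutive on the list, the most favourable case: 12-28%.
- 78 patients instead of 120, over all these patterns: 46-75%.
- Separate blocks of 9-15 for each therapist (the other possible reading): 5-6 patients would not complete a block, and 4-25% would still have an empty arm.

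**Effect on precision.** The protocol gives no therapist ICC, so .05, .10 and .20 are assumed. With a random therapist intercept, the variance of the PMI-NMI contrast is c′(X′V⁻¹X)⁻¹c. Perfect balance within therapist gives (1 − ICC) × 2/40. The ratio averages about 1.04 at ICC .05, 1.07-1.08 at .10 and 1.11-1.12 at .20. On the standard error, √1.04 = 1.02 and √1.12 = 1.06, so about 2-6%.

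**The case against.** The strongest reply is that the sentence is a hedged expectation placed directly after an admission that counts per therapist are not fixed, and that little follows from it. Much of this stands.

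- **Balance in expectation.** Under 1:1:1 allocation, expected counts are equal for every therapist. It would be wrong to say that near-equal counts cannot occur; the scheme simply does not control them. The hedge does not rescue the sentence, though, because it credits the block randomisation with the balance, and the blocks contribute almost nothing to it.
- **Bias.** A reader might infer that therapist differences bias the arm comparison. The protocol does not support that: patients are individually randomised, any therapist may deliver any condition, and therapist is level 3 of the model. The imbalance is chance, and its price is variance.
- **The main test.** Power is set for the time-by-condition interaction. Therapist differences in outcome level drop out of that test; only differences in slope matter. The 4-12% above is for a level contrast and should not be read as the loss in the interaction test.
- **Which therapists lose the key comparison.** A reader might take 24-40% as the share with no PMI-NMI comparison. That share counts any empty arm, including usual treatment. The relevant figure is about 16-28%.
- **Assumptions.** The range rests on an inferred centre-wide list and on unstated caseloads and assignment. This cuts both ways: consecutive assignment improves it, while unequal caseloads or fewer patients worsen it.
- **Choice of design.** Not stratifying by therapist at about five patients each is defensible, because balancing within therapist makes the next allocation easier to guess, and Design says therapists are not blind. That is a reason for leaving arm counts uncontrolled, but not for expecting them to be balanced.

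**Conclusion.** The point holds in a limited form. The balance per therapist expected in Design does not follow from the scheme, on either reading of how the blocks run. With 120 patients, near-equal caseloads and random assignment, about 24% of therapists (if 20) to 40% (if 25) would lack at least one arm, and about 16-28% would lack PMI or NMI.

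Overall arm balance and the validity of the randomised comparison are not in question. The loss is modest: about 4-12% in the variance of a PMI-NMI level contrast at the assumed ICCs, and for the interaction test only what therapist differences in slope add. The Innovations and Bias Minimization sections also put more weight on the cross-therapist design than the allocation supports. The model can adjust for imbalance, but it cannot supply within-therapist comparisons where an arm is empty.

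**What to change.** **Preferred.** If the therapist is known at allocation, let the independent assistant allocate by minimisation on therapist and overall arm totals, with a random element (for example, 80% probability of the arm that reduces imbalance). The protocol suggests the therapist is known: a therapist invites the patient to the diagnostic phase, study information is given in its first session, and arm-specific imagery training takes place during that phase. Keep therapist in the multilevel model. In simulation with near-equal caseloads this cut the share of therapists with an empty arm to about 0-3% when therapist carried most of the weight, and to about 3-10% when therapist and overall totals were weighted equally, so the weights should be fixed in advance.

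The cost is a script or spreadsheet in place of a fixed list, and somewhat greater predictability for unblinded therapists. The assistant should therefore keep the rule and the running counts concealed.

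**If the current scheme is kept.** Replace the expectation in Design with a statement that arm counts per therapist are not controlled and that some therapists will have no patient in one or more arms. Tone down the reliance on the cross-therapist design in Innovations and Bias Minimization. This costs only a change of wording.
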